#### T3 (12 months post-enrolment)

Participants will return to their GPs for a comprehensive assessment, completing a final lifestyle questionnaire. Participants will undergo blood tests to re-evaluate total cholesterol, HDL, LDL, triglycerides, glucose, and hemoglobin A1c levels. Moreover, participants will complete a questionnaire designed to evaluate the feasibility and acceptability of the interventions, including their experiences with the innovative interventions and their perceived utility. At T3, the GPs will also complete a questionnaire to assess the feasibility of the interventions from their perspective (Annex1, Section 7). Additionally, a sample of both GPs and patients will participate in qualitative interviews to provide insights on their experiences and observations throughout the study. A convenience sampling will be adopted to identify GPs and patients for the interview. The sampling will be done separately for the *four* trial arms trying to have a balance with respect to sex. A thematic framework will be used to develop the guide for the interviews, and the latter will be conducted by a group of trained professionals and recorded.

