**Methods:**

FitPreV is a pilot, four-arm, randomized controlled feasibility study involving 120 adults aged 40–69 years diagnosed with metabolic syndrome and an estimated 10-year CVD risk between 2.5 and 10%. Participants will be randomly assigned to: (1) standard counseling; (2) counseling plus WHD; (3) counseling plus PRS; or (4) counseling plus both PRS and WHD. Data will be collected at baseline, 1, 6, and 12 months. Feasibility indicators include recruitment and retention rates, acceptability, burden and structural readiness. Secondary outcomes include changes in lifestyle behaviors, lipid profiles and cardiovascular risk (SCORE2 algorithm).

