### Primary endpoints

The feasibility indicators as detailed in their section.

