### Feasibility indicators

Feasibility indicators are selected in line with commonly described domains in implementation research, including aspects of perceived usefulness, burden, and overall participant experience. In detail, to quantify the feasibility of the intervention, several indicators will be assessed:

Structural readiness
1.1 Experience of GPs in Clinical Studies: Prior experience of participating GPs in clinical research (Annex 1, section 7).1.2Availability of Necessary Tools and Facilities: This indicator assesses whether the general practices have the required resources to implement the interventions (Annex 1, section 7).Process feasibility
2.1 Recruitment rates: Proportion of participants who are successfully recruited for the study relative to the total number of eligible patients.2.2 Retention rates: Proportion of enrolled participants who remain in the study throughout its duration.2.3 Attendance rates: Proportion of scheduled sessions that participants attend compared to the total number of sessions they were expected to attend.Acceptability
3.1 Subjective Perceptions: Participants and physicians' perceptions of the intervention's feasibility and acceptability (20) (Annex 1, section 6).Validated questionnaires will assess participants' perceptions regarding:
Their understanding of cardiovascular risk.Perceived severity of CVD.Perceived benefits of the interventions.Perceived barriers to participation.Perceived benefits and barriers regarding the Polygenic Risk Score.Technology Acceptance Model (TAM) (29, 30): To evaluate the acceptability of wearable devices, participants will respond to questions based on the TAM (Annex 1, section 5) such as

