Ease of use of the devices.Usefulness of the devices in managing their health.Usefulness of the information regarding the Polygenic Risk Score.Intention to continue using the devices beyond the study period.BurdenBurden: The perceived burden of participation among participants and physicians. Both will be asked to evaluate whether the intervention's objectives are clear and if the time and effort needed for implementation are manageable within their daily routine (Annex 1, section 6 and 7).Participant capabilitySelf-Efficacy: Participant's beliefs in their ability to engage with the interventions effectively. Participants will respond to questions about their confidence in making lifestyle changes and managing their cardiovascular risk based on the information and tools provided during the study (Annex 1, section 6).

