### Criteria for progression toward a full trial

In line with methodological recommendations for feasibility studies, which emphasize the importance of prospectively defined progression criteria, this study includes predefined thresholds to guide decisions regarding progression to a future definitive trial (26, 31).

The following *a priori* progression criteria have been defined:

(a) **Recruitment:** At least 30% of eligible participants agree to participate and are randomized.

(b) **Completeness of outcome data:** Outcome data are available for at least 90% of participants, as recorded in the eCRFs.

(c) **GPs' willingness to participate:** At least 70% of participating GPs report that they would be willing to implement the study in routine practice.

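### Both structural readiness indicators rest on a GP questionnaire whose only stated time point is T3, so practices' starting resources would be known only after a year of delivering the trial

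*Protocol article*

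**What the plan says.** The Primary endpoints section refers the reader onward: "The feasibility indicators as detailed in their section". The abstract lists what these cover: "Feasibility indicators include recruitment and retention rates, acceptability, burden and structural readiness".

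The Feasibility indicators section defines structural readiness by two items, both drawn from the same instrument:

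- Indicator 1.1: "Prior experience of participating GPs in clinical research (Annex 1, section 7".
- Indicator 1.2: "This indicator assesses whether the general practices have the required resources to implement the interventions (Annex 1, section 7".

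The T3 section (12 months post-enrolment) says when that instrument is completed: "At T3, the GPs will also complete a questionnaire to assess the feasibility of the interventions from their perspective (Annex1, Section 7".

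The same annex section also carries part of the burden indicator, in which physicians judge whether "the time and effort needed for implementation are manageable within their daily routine (Annex 1, section 6 and 7".

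**The concern.** Readiness is most naturally read as what a practice brings to implementation: the experience and resources in place before the first participant is enrolled. Burden and willingness are different, since a GP can judge them only after delivering the interventions. The article places both kinds of item on a form given once, at the end.

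By then a GP has used the study materials, entered data in the eCRFs and carried out the six-month telephone follow-up. An answer about current resources may reflect what was acquired or learned during the year. An answer about the starting position depends on memory and may be coloured by how the year went. A GP who leaves, or who never enrols anyone, may give no answer at all, and that practice could be among the most informative about readiness.

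What is at stake is how a primary feasibility domain can be read. The Discussion promises evidence on organizational readiness and describes primary care as short of time and resources. A future trial team would want to know what practices had before they began.

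**Working it through.** No arithmetic applies. The article states no figure on this point: no number of GPs, no GP dropout and no readiness threshold. The check is a cross-reading of its sections.

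1. **Instrument.** Indicators 1.1 and 1.2 both cite Annex 1, section 7 (Feasibility indicators).
2. **Time point.** The T3 section assigns the GP questionnaire, citing the same annex section, to T3.
3. **Any earlier administration?** Pre-screening describes the record query, the invitation and the eligibility check. T0 describes consent, randomization and participant assessments. T1 describes communication of results. T2 describes a telephone follow-up of participants. None mentions a GP questionnaire or a practice assessment. T3 is therefore the only stated time point.
4. **Who would answer?** The visit schedule is counted from participant enrolment. A GP who enrols nobody has no T3 in that schedule, and the article does not say how such a GP, or one who withdraws, would be asked. Retention is defined for participants only: "Proportion of enrolled participants who remain in the study throughout its duration". No corresponding measure for GPs is given.
5. **How exposed is each item?**
   - Indicator 1.1 is a matter of history. It can be reported at T3 with little loss, provided the question excludes experience gained in this trial.
   - Indicator 1.2 describes a state that can change over the year. Asked about the present, it mixes starting resources with later ones. Asked about the past, it relies on recall.
   - Physician burden needs experience of delivery, so T3 suits it.
6. **Where does the result go?** Feasibility indicators are summarized descriptively (Statistical analysis). The three progression criteria concern recruitment, completeness of outcome data and GP willingness. The GP criterion reads: "At least 70% of participating GPs report that they would be willing to implement the study in routine practice". Readiness is not among them.

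Steps 1 to 3 establish the timing. Steps 4 and 5 show that the weakness falls mainly on indicator 1.2 and on GPs who may not reach T3. Step 6 limits the consequence to interpretation.

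**The case against.** The case for leaving the plan alone has several parts.

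- **The annex and the Figure 1 timeline are not shown.** The section 7 items may ask explicitly about the start of the study. This stands as a limit on what can be said. A retrospective wording would reduce the problem for 1.2, but the answer would still be open to hindsight.
- **The article does not define readiness as readiness at the start.** Indicator 1.2 asks whether practices have the resources, and GPs who have delivered the interventions may know better what was required. This is a fair argument for also asking at T3. It is not an argument against asking at activation.
- **Indicator 1.1 is historical.** This stands, with the proviso that this trial is excluded.

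A reader might also infer three stronger points, which the article does not support.

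- **That T3 cannot show readiness.** This goes too far: 1.1 can be recalled, and 1.2 can be reported retrospectively with some loss.
- **That T3 necessarily overstates readiness.** The direction is unknown. A year of delivery could equally expose missing resources and lower the answers.
- **That GPs who leave are excluded.** No rule says so and no GP attrition is reported. Missing answers from such GPs are a plausible risk, not a stated feature.

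Nor does the plan announce an analysis of recruitment by readiness that would be defeated. The GP-level summaries are meant to describe variability in recruitment, completeness and acceptability, and a T3 answer could still be linked to the same GP's figures, although the order of cause and effect would be harder to interpret.

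**Conclusion.** The point holds as a weakness of timing. As written, both structural readiness indicators depend on a form whose only stated time point is T3. Resources at the start, mainly indicator 1.2, would be learned only after a year of delivery, with exposure to hindsight and to change during the trial, and possibly not at all for a GP who withdraws or never enrols a participant.

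No size can be given, since the number of GPs, their attrition and the item wording are all unknown. The conclusion rests on two assumptions: that no earlier GP assessment exists outside the article, and that readiness is meant to describe the position before implementation. The effect is on how a descriptive primary indicator is interpreted. No progression criterion depends on it, so the decision on a full trial is not directly affected. The change is still worth making because it is cheap and because baseline answers become harder to recover as the trial proceeds.

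**What to change.** Split Annex 1, section 7 by time point.

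- Have every GP complete items 1.1 and 1.2 at activation, before that GP's first participant is enrolled. Report readiness for all activated GPs, including any who later withdraw or enrol nobody.
- Keep the burden, perception and willingness items at T3. Item 1.2 may be repeated there to capture resources that proved necessary in practice, reported separately from the activation answer.
- GPs already active should answer now with reference to the start of the study, leaving this trial out of 1.1. Flag these answers as retrospective.
- State both time points in the T3 and Feasibility indicators sections.

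The cost is a short extra form per GP and a small change to the data collection forms. It needs no additional participants or participant visits, and the descriptive analysis stays the same apart from the retrospective flag and, if 1.2 is repeated, a second time point.

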## Introduction

Cardiovascular diseases (CVDs) encompass a wide array of conditions, including coronary artery disease, heart failure, and stroke, which arise from the complex interplay of numerous genetic variants, unhealthy lifestyles and diet (1) and socioeconomic factors (2). CVDs pose a significant global health concern (3), as they are the leading cause of death and illness both in Europe and worldwide (4). Significant progress in CVDs management, coupled with heightened awareness of the value of preventive strategies, has contributed to a global decline in age-standardized incidence and mortality rates. Nevertheless, as the population ages and grows, the absolute number of CVDs incident cases and deaths has increased over time (5). A considerable portion of the burden of CVDs can still be attributed to modifiable risk factors, including elevated systolic blood pressure, high levels of LDL cholesterol, and tobacco use (6). This highlights the importance of sustained efforts in counteracting CVDs and in the development of innovative strategies for prevention (7). In this context, personalization represents a cutting-edge area of medical research, enhancing population health while potentially lowering expenses for healthcare systems. Polygenic risk scores (PRS) have recently attracted attention for their ability to quantify an individual's genetic predisposition to CVDs (8). By identifying subjects with high inherited risk, PRS could enable earlier and more targeted preventive interventions, complementing traditional risk stratification tools (8). This is particularly relevant for individuals with metabolic syndrome, a cluster of conditions including central obesity, dyslipidemia, elevated blood pressure and hyperglycemia, that markedly increases CVD risk (9). Such individuals represent a population in which combining genetic information with lifestyle monitoring could be particularly impactful, as an unfavorable polygenic architecture may synergize with metabolic and behavioral risk factors, thereby amplifying the lifetime cardiovascular risk trajectory and potentially accelerating the onset of major adverse cardiovascular events. Similarly, this population can take advantage of digital health technologies, such as wearable health devices (WHDs) capable of monitoring physical activity, dietary, and sleep habits giving the patient a feedback that could nudge him further toward healthy habits (10). Nevertheless, in order to facilitate the implementation of new health technologies and interventions, in addition to their efficacy currently under investigation in an ongoing trial (11), it is necessary to demonstrate their feasibility, considering factors that can prevent their adoption. These factors encompass among others, acceptability, demand, implementation, practicality (12), and their assessment can be useful for both refining methods to evaluate their efficacy and developing implementation strategies (13). To date, no study has evaluated whether PRS, alone or combined with WHDs, can be feasibly adopted within primary prevention programs for CVDs. The present paper describes the rationale and design of the FitPreV trial, a feasibility pilot randomized controlled study assessing the integration of PRS and WHDs in primary prevention for individuals with metabolic syndrome within the Italian National Health Service (SSN).

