## Interventions

### Genetic testing

Genotyping is planned for participants in groups 3 and 4 to support the calculation of of a commercially available genome-wide PRS, provided by an external provider. Genotyping will be performed using Illumina microarray technology (21), a cost-effective platform for large-scale SNP profiling in disease and population genetics studies. This approach generates data on millions of genetic variants per individual. Missing genotypes will be imputed using a modified version of the GLIMPSE algorithm (22), leveraging reference panels from the 1,000 Genomes Project (23) to ensure high-quality genome-wide coverage.

The PRS was developed and validated in large, ancestrally diverse cohorts (totaling over 29,000 individuals across multiple genetic ancestry groups, including European, African, South Asian, and others), demonstrating robust predictive performance (odds ratio per standard deviation of approximately 1.57) (24).

The resulting CVD genetic risk profile will be communicated to clinicians (and subsequently to participants) using a three-tier classification based on the participant's PRS percentile rank within the population distribution:

**Normal risk:** PRS below the 75th percentile.**Moderate risk:** PRS between the 75th and 97th percentiles (approximately 2-fold increased risk compared to the population average).**High risk:** PRS at or above the 97th percentile (top 3% of the population; approximately 3-fold increased risk compared to the population average).

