### Statistical analysis

Randomization will be performed using a computer-generated sequence with randomly permuted blocks with random block sizes and block order. Allocation sequences will be securely stored, and participants will be assigned to their study group after a 1:1:1:1 randomization. The arm assignment will be centrally provided through REDCap platform.

As this is a feasibility study and not designed to assess clinical efficacy, no formal power calculation has been performed, in line with the CONSORT extension for randomized pilot and feasibility trials (26). The sample size has instead been determined based on practical considerations and the need to assess key feasibility outcomes, including recruitment, retention, adherence, and data completeness. While no formal minimum sample size is established for feasibility studies, small sample sizes have been suggested in the literature (27). A total of 120 participants is considered sufficient to provide informative estimates of these parameters and to support the design of a future definitive trial (28).

Feasibility indicators will be summarized using descriptive statistics: absolute and relative frequencies for categorical variables and means with standard deviations or medians with interquartile ranges for continuous variables. Where appropriate, 95% confidence intervals will be reported. Missing data patterns will be described without imputation, as recommended for feasibility designs. Feasibility outcomes will also be summarized at the GP level to explore variability in recruitment, data completeness, and acceptability across practices.

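### Interviewees in the PRS arms are chosen by convenience within arm and sex, without regard to PRS tier, although only about 15 of the 60 can be expected to receive an elevated result and about 2 a High one

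*Protocol article*

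**What the plan says.** All references are to the protocol article.

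- **Numbers.** The Statistical analysis section sets the total: "A total of 120 participants is considered sufficient to provide informative estimates of these parameters". It also sets equal allocation: "participants will be assigned to their study group after a 1:1:1:1 randomization".
- **Who gets a PRS.** Genetic testing section: "Genotyping is planned for participants in groups 3 and 4".
- **How the result is graded.** The same section uses the "participant's PRS percentile rank within the population distribution" to form three tiers. Normal is below the 75th percentile. Moderate is the 75th to 97th, described as about 2-fold risk. High is "PRS at or above the 97th percentile (top 3% of the population; approximately 3-fold increased risk compared to the population average". The inclusion and exclusion criteria do not select on PRS.
- **Who is interviewed.** T3 section: "A convenience sampling will be adopted to identify GPs and patients for the interview". Sampling is done separately for the four "trial arms trying to have a balance with respect to sex". The number of interviews is not given.
- **What is summarised.** Feasibility indicators, which are the primary endpoints, are summarised descriptively and also by GP. They include perceived benefits and barriers of the PRS. No summary by tier is mentioned.
- **Why PRS is studied.** Introduction: "By identifying subjects with high inherited risk, PRS could enable earlier and more targeted preventive interventions".

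**The concern.** Someone told Normal and someone told that their risk is about two or three times the average have had quite different disclosures. The Introduction justifies PRS by the second kind of person. The Discussion lists making polygenic risk understandable and actionable among the anticipated challenges. The tier is thus the characteristic that best describes what a PRS participant went through, yet the interview plan names its balancing factors and leaves the tier out.

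The interviews are the only part of the study that can explore in depth how an elevated result was received, and they take place at 12 months. If elevated-tier people are missed then, their accounts will be hard to recover. An overall acceptability figure for the PRS will be weighted mainly to people who received a reassuring result, so it can look favourable even if those with an elevated result were much less satisfied.

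**Working it through.** The protocol gives no expected tier counts, so there is no stated figure to reproduce.

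**Inputs from the document.** 120 participants, four equal arms, PRS in two of them; tier shares 0.75, 0.97 − 0.75 = 0.22, and 0.03.

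**Assumption.** Participants follow the population PRS distribution (relaxed in step 3).

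**1. Expected counts.** PRS participants: 120 × 2/4 = 60, or 30 per arm.

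| Tier | Share | Expected of 60 | Central 95% binomial range | Expected per arm of 30 |
|---|---|---|---|---|
| Normal | 0.75 | 45.0 | 38 to 51 | 22.5 |
| Moderate | 0.22 | 13.2 | 7 to 20 | 6.6 |
| High | 0.03 | 1.8 | 0 to 5 | 0.9 |
| Moderate or High | 0.25 | 15.0 | 9 to 22 | 7.5 |

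**2. Chance of no High result.** Both PRS arms: 0.97^60 = 0.161. One arm: 0.97^30 = 0.401. The chance of at most one High result among 60 is 0.459.

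**3. Sensitivity to enrichment.** People with metabolic syndrome might have a higher mean PRS. For assumed upward shifts of the mean, the Normal/Moderate/High counts among 60 are:

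- 0.1 SD: 43.0 / 14.7 / 2.2
- 0.3 SD: 38.8 / 17.8 / 3.4
- 0.45 SD: 35.3 / 20.1 / 4.6

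Normal remains the majority and High remains a handful.

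**4. Interviews.** The number is not stated, so a range is shown. If selection is unrelated to tier, the chance that none of k PRS-arm patients has an elevated result is 0.75^k, and that none has a High result is 0.97^k.

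| k | No elevated result | No High result |
|---|---|---|
| 5 (for example one arm) | 24% | 86% |
| 10 (for example 5 in each PRS arm) | 6% | 74% |
| 20 | 0.3% | 54% |

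**5. Weight of the Normal tier.** 45/60 = 75% of any overall PRS figure. As an illustration with invented rates, 90% acceptance in Normal and 40% in Moderate or High gives (45 × 0.90 + 15 × 0.40)/60 = 46.5/60 = 77.5% overall.

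**6. What a split by tier could show.** Illustrative Clopper-Pearson 95% intervals: 36/45 gives 65% to 90%; 12/15 gives 52% to 96%; 1/2 gives 1% to 99%. Normal against Moderate or High can be described, though imprecisely. The High tier alone cannot be estimated.

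**The case against.** Several points on the other side are sound, and they limit how far the finding goes.

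- **Elevated results are not absent.** A reader might infer from the 2 expected High results that the study can say almost nothing about giving people an elevated risk. The document does not support this. Moderate is itself described as about 2-fold risk, so about 15 of 60 receive an elevated result. All participants are asked to complete the T3 feasibility and acceptability questionnaire, whoever is interviewed. Only the High tier is barely observable.
- **Pooling by arm is not stated.** A reader might infer that PRS acceptability will be reported by arm only. The article names no tier table, but it does not exclude one, and a statistical analysis plan that is not shown could contain it. The point about interview sampling does not depend on this, because the article itself fixes the sampling method.
- **The progression decision does not use the figure.** The three criteria are recruitment, completeness of outcome data and GP willingness. None uses patient acceptability of the PRS, so the choice of interviewees does not bear directly on the decision to proceed.
- **The natural mix has meaning.** In an unselected metabolic syndrome population about three quarters would be told Normal in practice too. An overall figure is a fair answer about that setting and should be kept.
- **No genotyping in groups 1 and 2.** This rules out a randomised comparison within tier, but for a feasibility aim that is not a fault.
- **Access to genetic data.** Inviting by tier could spread genetic results to interview staff, while the data management section calls for restricted access. This is a fair caution, but the Genetic testing section already has the result go to clinicians, so the GP can make the invitation.

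The limitations paragraph concedes self-selection among interviewees. It does not mention tier mix.

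**Conclusion.** The point stands in a limited form. By the plan's own cut-offs about 45 Normal, 13 Moderate and 2 High results are expected among 60, with a 16% chance of no High result. Convenience sampling within arm and sex leaves the presence of elevated-tier interviewees to chance. How large that chance is depends on a number of interviews that the article does not give: with an assumed 5 patients per PRS arm, an arm has none with probability 24%, and both arms together have none with probability 6%. With 20 interviewees the risk of having none with an elevated result almost vanishes, but the chance of having nobody from the High tier is still about one half. The counts rest on the population PRS distribution, and a modest upward shift does not alter the conclusion. The change is worth making because it improves the answer to the PRS question at almost no cost; the feasibility design as a whole is not undermined.

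**What to change.** **Main change (T3 section).** In groups 3 and 4, replace convenience sampling of patients with purposive sampling by PRS tier, within the same number of interviews. Invite every High-tier participant and deliberately include Moderate-tier ones, keeping the attempt at balance by sex. Have the GP make the invitation, so that access to genetic data is not widened.

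**Low-cost addition (Statistical analysis and Feasibility indicators sections).** Describe the PRS perception, burden and self-efficacy items for Normal versus Moderate or High, alongside the overall figure. State in advance that no conclusion about High-tier disclosure will be drawn if only a few such results occur.

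**Cost.** Protocol wording and one descriptive table; no extra participants or interviews. The drawbacks are small elevated-tier counts (about 15, range 9 to 22) and an interview sample that no longer mirrors the natural tier mix, which the report should say. Purposive sampling also cannot supply High-tier people if none occur.
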